#### Missed sessions and homework

AB will record attendance and make notes on participation. Details of issues covered and homework engagement will be recorded as well. In the case of non-attendance at sessions, AB will contact the participant to ascertain the problem and to discuss a suitable solution addressing any concerns. Unfortunately, because of the group setting of this intervention, participants will not have the opportunity to reschedule a missed session.

Participants will be asked to keep a diary (provided with the manual) of their weekly homework mindfulness practices. A record of homework engagement will be kept, and final analyses will control for homework compliance.

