### Mindfulness-based intervention for PD

The MBI will be delivered in eight sessions over an 8-week period. The sessions will last 1 h and will be held via videoconference through Skype, an online application, in groups of five people. The videoconferences will be initiated by AB and will be arranged at a day and time that is most suitable for all participants in the group. CDs with homework mindfulness practices will address potential issues people with PD may come across during practices, like resting tremor, spasms, fatigue, and mind wandering.

The sessions will be carried out based on a written manual. However, flexibility will be allowed to follow issues and topics that are more important for the group during the sessions. Participants will be issued the mindfulness manual before their first session and will be encouraged to read only the chapter of the relevant session each week. The manual will contain eight chapters. In each chapter, the homework for each week will be outlined followed by a brief description of the week’s theme.

Participants will sign a consent form indicating that they understand that they are being recorded and that recordings will be stored in password-protected files and only be used for the stated purposes (i.e. fidelity checks and supervision).

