### Data analysis plan

#### Quantitative analysis plan

Statistical analysis will be carried out in STATA. Descriptive statistics (mean, median, standard deviation) will be calculated for all demographics and clinical variables. All group comparisons will be carried out on an intention-to-treat basis, that is participants will be analysed in the group to which they were randomised. Descriptive results concerning recruitment numbers, completions, drop-out rates, and missing data will be calculated and reported. The quantitative data will be summarised with standard descriptive measures for each group separately to determine potential change within group over time. Continuous variables will be summarised by their mean and standard deviation, categorical variables as numbers and percentages, and presented with 95% confidence intervals. With the aim of identifying a potential response shift in some of the participants, a retrospective measurement will also be implemented. In particular, then-test questions will be added to the post-intervention and 20-week follow-up questionnaires for several outcome variables. Both measurements of the effect of the course (prospective and retrospective) will be compared, in order to add robustness to the results. We will also assess the sensitivity of the results to excluding patients who did not receive a sufficient number of MBI sessions or those who had little meditation home practice.

**Table 3 Tab3:** Topic guide for participants’ experiences with the mindfulness course

Questions	Prompts
1. First of all, can you start by telling me what you were expecting from the mindfulness sessions?	-What did you think the programme would be like? -In what ways (if any) did you think it might help you?
2. How did you find the programme overall?	-Tell me how you found your first session -Tell me about the other sessions -Tell me how you found the homework tasks
3. Can you tell me what you liked about the programme?	-What was helpful? Why? How? -Were there some sessions/some aspects that were more helpful than others?
4. Can you tell me what you disliked about the programme?	-What was unhelpful? Why? How? -Were there some sessions/some aspects that were less helpful than others?

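### The unrestricted promise to control the final analyses for homework compliance conflicts with the intention-to-treat comparison of the arms

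*Protocol article*

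**What the plan says.** Two parts of the protocol article bear on this.

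- **Missed sessions and homework:** "A record of homework engagement will be kept, and final analyses will control for homework compliance". No model, outcome, arm or secondary status is attached to the sentence.
- **Quantitative analysis plan:** "All group comparisons will be carried out on an intention-to-treat basis, that is participants will be analysed in the group to which they were randomised". No homework covariate is mentioned. Outcomes are to be summarised by "standard descriptive measures for each group separately to determine potential change within group over time". The same section adds a sensitivity analysis "excluding patients who did not receive a sufficient number of MBI sessions or those who had little meditation home practice".

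Comparing the MBI group with the WLC group on each outcome is one of the listed Aims.

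On where homework data come from: "Participants will be asked to keep a diary (provided with the manual) of their weekly homework mindfulness practices", and "Participants will be issued the mindfulness manual before their first session". Booking in participants' groups says that wait-list participants are to be discouraged from new mindfulness activity. Wait-list control group offers them the course only once the week-20 follow-up is over. Table 2 schedules home practice at weeks 8 and 20 and does not separate the arms.

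**The concern.** Home practice is a component of the treatment. It is set each week, recorded after randomisation, and available only to those who were given the course. Used as a covariate in an arm comparison, it has two faults. It lies on the path from allocation to outcome, so adjusting for it removes whatever benefit works through practice. It is also nearly a copy of the allocation, so the arm coefficient becomes imprecise and rests on extrapolation to MBI participants who do no practice.

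The result would not be the effect that the Quantitative analysis plan promises. The Discussion makes a grant application for the main trial depend on the intervention looking feasible and potentially effective. The Economic evaluation plan combines costs with HADS. A homework-adjusted difference could misinform both.

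**Working it through.** The article states no figure on this point, so there is none to reproduce. The documents give only 60 participants allocated 1:1, that is 30 per arm. All other inputs are assumptions. Benefit is counted as positive, in outcome SDs.

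**1. Is homework confined to one arm?** The diary comes with the manual, and the manual precedes the first session. WLC participants are discouraged from practising and get the course only after week 20. Current meditators are excluded at entry. Homework is therefore zero or undefined in the WLC arm. This is an inference, since no sentence says it outright.

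**2. What the adjusted arm coefficient estimates.** Let m and s be the mean and SD of practice in the MBI arm, with zero practice in WLC. In a regression of outcome on arm and homework, the homework slope b comes from the MBI arm alone, and

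arm coefficient = (MBI mean − WLC mean) − b × m.

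This is MBI at zero practice against WLC. If a share p of a true effect T acts linearly through practice, b = pT/m and the coefficient is (1 − p)T. With T = 0.5:

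- p = 1: 0.00
- p = 0.5: 0.25
- p = 0: 0.50

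Simulations of 5,000 runs (practice mean 5, SD 2, baseline-outcome correlation 0.6) gave about 0.00, 0.25 and 0.51. Without homework in the model they gave about 0.50.

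**3. Loss of precision.** With 1:1 allocation, the between-arm variance of homework is 0.25 × m² and the mean within-arm variance is 0.5 × s². For m = 5 and s = 2 these are 6.25 and 2. So R² = 6.25/8.25 = 0.758, VIF = 1/(1 − 0.758) = 4.1, and the standard error is multiplied by √4.125 = 2.03. In general VIF = 1 + m²/(2s²):

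| m/s | VIF | SE multiplied by |
|---|---|---|
| 1.5 | 2.1 | 1.46 |
| 2 | 3.0 | 1.73 |
| 2.5 | 4.1 | 2.03 |
| 3 | 5.5 | 2.35 |

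In simulation at m/s = 2.5 the standard error rose from 0.21 to about 0.45–0.49.

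**4. If practice also relates to prognosis.** Let r be the correlation of practice with outcome that is due to prognosis. The slope b gains r/s, so the coefficient becomes (1 − p)T − r × m/s. A second simulation used m/s = 2 and a prognostic factor correlated 0.5 with outcome. Practice was correlated 0, 0.3 or 0.5 with that factor, so r = 0, 0.15 or 0.25 and the shift is 0, −0.30 or −0.50. Simulated arm coefficients:

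| True effect | Share through practice | 0 | 0.3 | 0.5 |
|---|---|---|---|---|
| 0 | – | 0.00 | −0.30 | −0.50 |
| 0.5 | 0 | 0.49 | 0.20 | −0.01 |
| 0.5 | 0.5 | 0.25 | −0.06 | −0.26 |
| 0.5 | 1 | 0.01 | −0.30 | −0.51 |

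The comparison without homework recovered the true effect throughout (standard error about 0.26, against about 0.46 with homework). If people with a worse prognosis practise more, r is negative and the shift goes the other way.

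**5. The exclusion analysis.** Dropping the lowest fraction q of MBI participants by engagement, with engagement-outcome correlation r and no true effect, gives an apparent benefit of r × φ(z_q)/(1 − q).

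- q = 0.25: the factor is 0.424, giving 0.13 (r = 0.3) to 0.21 (r = 0.5).
- q = 0.30 in the second simulation, where r is 0.15 and 0.25: 0.07 and 0.12.

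The two ranges differ mainly because the second defines the correlation with a prognostic factor and not with the outcome itself.

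**The case against.** The strongest reply is that no two-arm regression with homework appears in the article. The planned summaries are descriptive and by group, and the practice diary is listed among the process mechanism measures. The sentence could mean a dose analysis within the MBI arm, a mechanism analysis, or simply the low-practice exclusion. This stands in part: the figures above apply only if homework enters the arm comparison. But the sentence speaks of final analyses without limit, and the arm comparison is an aim, so a reader following the text could do exactly that.

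It is also fair that the feasibility criteria (recruitment, retention, adherence) are untouched, and that the Discussion sets no efficacy threshold that a distorted estimate could cross. That limits the consequence.

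A reader might go further and infer two things that the documents do not support:

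- **That the exclusion analysis also abandons intention-to-treat.** It does not. The text introduces it as an addition: "We will also assess the sensitivity of the results to excluding patients who did not receive a sufficient number of MBI sessions". It stands beside the intention-to-treat comparison and replaces nothing. Its cut-offs may properly sit in a fuller document.
- **That the homework-adjusted estimate is bound to be biased.** When practice carries none of the effect and is unrelated to prognosis, the bias is nil and only precision suffers.

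**Conclusion.** The sentence on homework is wrong as written. Applied to the MBI-versus-WLC comparison, it contradicts "All group comparisons will be carried out on an intention-to-treat basis" in substance: participants stay in their randomised arms, but the coefficient no longer estimates the effect of allocation. For a true benefit of 0.5 SD, the estimate lies between about 0 and 0.5 SD with roughly double the standard error. It goes lower or changes sign if better-prognosis participants practise more. These sizes rest on assumed practice levels, effect and correlations, on linearity in practice, and on the inference that wait-list homework is absent. The exclusion analysis is a lesser matter of labelling. Severity: moderate.

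**What to change.** 1. Under Missed sessions and homework, delete the clause on controlling for homework compliance. Alternatively, restrict it to a descriptive summary of homework dose against change within the MBI arm, labelled as non-randomised.
2. In the Quantitative analysis plan, state that between-arm comparisons adjust for no variable measured after randomisation.
3. Keep the low-attendance and low-practice exclusion as a sensitivity analysis beside intention-to-treat. Label it exploratory and prone to selection bias, because only MBI participants can be excluded while the wait-list arm stays whole.
4. A complier-average causal effect analysis is an optional addition. If used, state its exclusion restriction: allocation has no effect on participants below the receipt cut-off. This is doubtful for people who attend a few sessions and hold the manual and CDs, and a failure could inflate the estimate.

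The cost is a few sentences of text. No new data are needed, and the diary data are still reported.

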### Wait-list control group

9pt?>Participants allocated to the WLC group will receive the treatment they would normally expect from the National Health Service (NHS) in the UK. People may receive a mix of clinical input and review from both primary and secondary care providers, according to individual health needs. Access to psychological assessment and intervention for people with PD is inconsistent across the UK, and dedicated psychological services are extremely scarce [29]. People in the WLC group will be offered the opportunity to take part in the MBI at the end of the 20-week follow-up.

### Assessments

[name], the trial coordinator, not involved in the therapy sessions, will coordinate all the assessment procedures. As shown in Table 2. Participants will be asked to complete a set of standardised questionnaires online or on paper, depending on their preference, at four time points (baseline, mid- and end of the intervention, and 3 months after completing the intervention). If participants are unable to use a keyboard or write on paper, they will have the option of completing assessments by telephone.

#### Screening measure

Telephone Interview for Cognitive Status Instrument modified version (TICS-M, [26]). This 13-item instrument will be used to assess cognitive status over the phone. Although this screening tool gives particular emphasis on learning and memory, items probing orientation, repetition, naming, and calculation are also included. The total score ranges from 0 to 50, with higher scores indicating better cognition. A total score cut-off of 20 will be used to deem participants eligible to take part in the study.

#### Feasibility outcomes

Feasibility outcome measures have been decided following Thabane et al. [30] recommendations.

We will compare the actual recruitment rate to the target recruitment rate, which is 10 participants per month, and also compare the actual recruitment rate to recruitment rates of psychological trials in PD. We will also compare the retention/refusal and adherence rates to other psychological trials in PD as well as mindfulness interventions in PD delivered face-to-face. We will consider the trial feasible if these processes compare favourably to other psychological trials or mindfulness trials in PD. We will also assess the appropriateness of the eligibility criteria in recruiting a population receptive to, and appropriate for, a mindfulness intervention by assessing adherence and retention rates. We will assess whether the criteria were too restrictive by comparing recruitment targets against actual recruitment process and also assessing whether too many people were excluded based on specific criteria.

We will assess time and resource problems that can occur during the main study by assessing the length of time required to fill out all the questionnaires. We will investigate whether there is participant overload, how much time it takes to screen participants and mail out consent forms, whether Skype equipment is needed, and how problems with installing or using Skype can best be managed.

We will also investigate issues around data collection, whether data from different data points can be matched, whether diary entries can be logged accurately, whether there are important data variables left blank, or whether the data show too much or too little variability.

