## Methods/Design

### Design and theoretical framework

We will use a parallel group randomised controlled design. A total of 60 participants with PD will be randomly assigned to either an 8-week MBI course (*n* = 30) or a WLC (*n* = 30). CONSORT flow chart of the study is summarised in Fig. 1.

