### Participants

#### Study sample

A pilot phase II trial of at least 30 participants is considered adequate for obtaining reasonably reliable sample size estimates [24]. We aim to recruit 60 people affected by PD. This sample will allow us to include six intervention groups to estimate intraclass correlations that relate to the fact that we are treating people in groups rather than individually.

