#### Recruitment and consent process

Potential participants affected by PD are recruited through adverts on the Parkinson’s UK website and the Michael J. Fox Foundation. Recruitment started in February 2016 and is expected to finish in June 2016.

People with PD who see the web advert or the email during the trial period and are interested in the study will get in touch with the trial coordinator. Participants will receive adequate information before consenting to take part in the study, including information sheets and discussion with the trial coordinator. Potential participants will be issued with a Participant Information Sheet and will be encouraged to read it carefully and to discuss it with others before making a decision. Participants will also be encouraged to contact the researchers with any questions that they might have. In the initial discussion with the participant, the trial coordinator will check whether the participant has understood the purpose and nature of the research and what the research involves, its benefits (and lack of benefits), risks, and burdens. After the initial discussion with the trial coordinator and consideration of the information sheets, potential participants will have at least 24 h to fully consider the implications of taking part in the research, ask questions, and reflect, before giving consent. Individuals participating in the study will sign a written consent form before the baseline assessments. On the form, participants are given the choice to consent to the mindfulness trial and questionnaire assessments only or to an additional in-depth telephone interview after their mindfulness programme has been completed.

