#### Randomisation

Participants will be randomly assigned to either the MBI group or the WLC group with a 1:1 allocation using a computer-generated blocked randomisation scheme. The randomisation scheme will be generated using the randomization.com website http://www.randomization.com. Block randomisation will allow keeping groups in similar sizes, ensuring a balance of numbers in each group at any time during the trial. Six blocks of 10 participants each will be used. The parameters will be saved for our records.

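### The target recruitment rate of 10 per month does not match 60 participants by the expected June 2016 finish: five full months at that rate give at most 50

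*Protocol article*

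**What the plan says.** Three statements in the protocol article bear on this point.

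- **Rate.** Feasibility outcomes says the team will "compare the actual recruitment rate to the target recruitment rate, which is 10 participants per month". The same section also compares recruitment targets with actual recruitment to judge whether the eligibility criteria were too restrictive.
- **Window.** Recruitment and consent process says: "Recruitment started in February 2016 and is expected to finish in June 2016".
- **Number.** Study sample says: "We aim to recruit 60 people affected by PD". Design and theoretical framework repeats the 60, with 30 per arm.

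The 60 is also built into the structure of the trial. Study sample says: "This sample will allow us to include six intervention groups to estimate intraclass correlations". Randomisation says: "Six blocks of 10 participants each will be used". The intervention section sets groups of five.

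The overall feasibility rule is a separate statement: "We will consider the trial feasible if these processes compare favourably to other psychological trials or mindfulness trials in PD". The article gives no second rate, no other recruitment period and no extension.

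**The concern.** A target rate, a recruitment period and a planned number are tied together: the first two multiplied should give the third. Here they do not, and the gap runs in the lenient direction, because the rate is lower than the one the plan needs.

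This matters more than it would in a conventional trial. The first specific aim of this pilot is to measure recruitment and related rates so that the main trial can be planned, and 10 per month is the only numeric comparator for recruitment in the article. If recruitment ran at exactly that rate, the report could say it was on target while the planned number had not been reached by the planned date. The question about the eligibility criteria would be affected too. Judged by the rate, the criteria would look suitable; judged by 60 by June, they might look too restrictive. The article does not say which target decides.

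**Working it through.** **Inputs, all from the protocol article**

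- Target rate: 10 participants per month (Feasibility outcomes).
- Window: February to June 2016, start and finish days not given (Recruitment and consent process).
- Planned number: 60 (Study sample; Design and theoretical framework).

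I assume that the rate counts people who go towards the 60. The article says participants per month and does not say whether that means consented or randomised. If some of the 10 per month were never randomised, the gap would be wider.

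**Step 1. Try to reproduce the 60.** Expected number = rate × months.

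| Reading of the window | Months | Number at 10 per month | Rate needed for 60 |
|---|---|---|---|
| Both end months in full | 5 | 10 × 5 = 50 | 60 / 5 = 12 |
| Exact days, 1 February to 30 June (151 days / 30.4375) | 4.96 | 49.6 | 12.1 |
| Mid-February to mid-June | about 4 | about 40 | about 15 |
| Shortest, 29 February to 1 June (94 days / 30.4375) | 3.1 | about 31 | about 19 |

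No reading gives 60. The first row is the most generous, so 50 is the upper bound on what the target rate yields in the stated window. The shorter readings assume days that the article does not give; they show only that the gap cannot be closed by reading the dates differently.

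**Step 2. Size of the gap on the most generous reading.** 60 − 50 = 10 participants, and 10 / 60 = 17%. As a rate, the benchmark is 12 − 10 = 2 per month too low for the stated plan.

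**Step 3. What would reconcile the figures.** At 10 per month, 60 / 10 = 6 months, which is February through July. Within February to June, the rate must be at least 60 / 5 = 12 per month.

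The sample size is not based on power, so no alpha, effect size or power calculation enters the check.

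**The case against.** The strongest reply is that the three figures are of different kinds. The 60 is a plan, 10 per month is a comparator for what is observed, and June is a forecast, worded as an expectation and written once recruitment was under way. A trial that recruits faster than its target can have a target of 10, finish in June and enrol 60. The article does not say that this was happening, but it does not exclude it. This stands: the documents show a mismatch between target rate and expected date, not a strict impossibility.

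Two stronger readings are tempting, and the documents support neither.

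- *The trial would close one block short.* A reader might infer that recruitment at 10 per month would end with 50 participants, five blocks and five mindfulness groups, weakening the intraclass correlation estimate. But nothing makes June a stopping date, while 60 participants and six blocks of 10 are stated as fixed. If recruitment ran at exactly 10 per month, the plan reads more naturally as slipping into July.
- *The trial would pass a feasibility criterion that is too easy.* A reader might take 10 per month as a pass mark. The stated rule is a favourable comparison with other trials, and no pass mark is attached to the rate. Recruitment numbers are also to be reported, so a shortfall from 60 would be visible.

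It can also be said that little would be lost even at 50, because Study sample regards at least 30 participants as adequate for a pilot. That limits the seriousness of the point but does not make the figures agree. Nor can a probability of reaching 60 by June be taken from the documents: it would need an accrual model and a hard cutoff, and neither is stated.

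**Conclusion.** The point holds in a limited form. At the target rate, the expected window yields at most 50 of the planned 60, a gap of 10 participants (17%). The benchmark is 2 per month below what 60 by June requires. This follows from the article's own figures and needs only the assumption that the rate counts people towards the 60; counting both end months in full already favours the plan.

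The likely practical consequence is about one extra month of recruitment, not a smaller trial. The consequence for interpretation is that recruitment could match the rate benchmark and still be behind plan, in a pilot meant to inform the recruitment assumptions of the main trial. That is minor to moderate, and worth correcting because it costs so little.

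**What to change.** Reconcile the three figures in one of two ways.

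1. Keep 10 participants per month and state July 2016 (six months) as the expected end of recruitment.
2. Keep June 2016, state that 60 by then needs about 12 per month, and use that rate as the benchmark.

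In either case, say that recruitment and the eligibility criteria will be judged against the reconciled rate. It would also help to say whether the rate counts consented or randomised participants.

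The first option changes one date and leaves the benchmark alone. The second changes one number and makes the benchmark harder to meet. Because recruitment had already started, the second also alters a comparator while data are accruing, so the original 10 per month should be reported alongside it. Neither option affects the sample size, the randomisation or the intervention.

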To date, there is very little research in evaluating the effects of mindfulness in reducing anxiety and depression in patients with PD. Given the body of evidence exposed above, it would be realistic to expect that a mindfulness-based intervention could be beneficial for people with PD in relation to issues such as denial and acceptance of the illness, the loss of independence, and the many disturbances that go together with a disease over which the person has limited control.

We propose to deliver a mindfulness intervention via Skype, an online application that enables videoconferences with two or more people. Online mindfulness courses might facilitate attendance and adherence in this particular population [17]. There has been increasing use of distance-delivered interventions for people with disease-related barriers such as impaired mobility. Further, there is evidence that distance-delivered mindfulness interventions can also be effective in people with chronic medical conditions [20–23].

We ran two patient advisory group meetings (*n* = 14) with people with PD in preparation for this trial. Participants of these meetings were recruited through Parkinson’s UK research network and most had some knowledge of mindfulness and its application. The first and second authors facilitated the groups. We talked to participants about our plans with the trial and the development of the intervention, and here, we incorporated their feedback. The focus group participants talked about mindfulness being beneficial to people who do not necessarily experience high levels of anxiety or depression but still they have difficulties adjusting to PD challenges and managing PD symptoms. Participants also reported that although using Skype may exclude people not familiar with technology or people who do not own a computer, this method of delivery would make it possible for people across the country and those with restricted mobility to participate. Patient advisory group participants were overall in favour of using Skype and as one participant said ‘we need to move with the times, we need to go with the technology’.

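### Recruitment against target does not measure how restrictive the criteria are, and the home computer/internet criterion cannot be judged from exclusions among people recruited online

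*Protocol article*

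**What the plan says.** Under Aims, the protocol article lists the appropriateness of the eligibility criteria among the things to be monitored for planning the main trial. Feasibility outcomes says how restrictiveness will be judged, in one sentence with two parts. The first part reads: "We will assess whether the criteria were too restrictive by comparing recruitment targets against actual recruitment process". Its yardstick is "the target recruitment rate, which is 10 participants per month". The second part turns to exclusions: "and also assessing whether too many people were excluded based on specific criteria".

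Inclusion criteria require a computer and an internet connection in the home. Under Recruitment and consent process, participants "are recruited through adverts on the Parkinson’s UK website" and through a second foundation whose medium is not stated. Those who then contact the coordinator are described as "People with PD who see the web advert or the email during the trial period". No offline route is described.

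The Background reports that the patient advisory groups had already raised the access barrier: "using Skype may exclude people not familiar with technology or people who do not own a computer". The limitations paragraph in the Discussion does not return to it. The Discussion looks ahead to a main trial on a representative sample.

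**The concern.** Two parts of the stated method do not carry the conclusion they are meant to support.

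- **Recruitment against target.** How many people join each month depends on how many see the advert, how many respond and how many consent, as well as on how many are eligible. Wide reach can hide strict criteria, and poor reach can make reasonable criteria look strict.
- **Exclusions on the access criterion.** The recruitment route selects on nearly the same characteristic as the criterion. People without home access are mostly lost before anyone can record them as excluded.

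At stake is what the pilot may say on a stated aim. A met target together with a near-empty row for home access could be read as evidence that the criteria, including this one, are not too restrictive. For home access the pilot would have had little chance of observing anything else.

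**Working it through.** **1. The plan's own figure.** The target rate is 10 per month. Recruitment runs over the period given by "Recruitment started in February 2016 and is expected to finish in June 2016", at most 5 calendar months, and the goal is "We aim to recruit 60 people affected by PD". Then 10 × 5 = 50, not 60. Reaching 60 needs 60/10 = 6 months, or 60/5 = 12 per month. This mismatch is a separate matter, but it shows that recruitment against target is not a clean yardstick even for recruitment.

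**2. What a met target reveals.** Recruits per month = enquiries × eligible share × consent share. The documents give none of the three factors, so the values below are assumptions.

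| Consent share | Eligible share | Enquiries per month needed for 10 recruits | Of these, ineligible per month |
|---|---|---|---|
| 100% | 90% | 10/(0.9 × 1.0) = 11.1 | 1.1 |
| 100% | 20% | 10/(0.2 × 1.0) = 50.0 | 40.0 |
| 80% | 90% | 10/(0.9 × 0.8) = 13.9 | 1.4 |
| 80% | 20% | 10/(0.2 × 0.8) = 62.5 | 50.0 |
| 60% | 90% | 10/(0.9 × 0.6) = 18.5 | 1.9 |
| 60% | 20% | 10/(0.2 × 0.6) = 83.3 | 66.7 |

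Every row meets the target exactly, so the target alone does not identify the eligible share. The last column does: exclusion counts tell lenient criteria from strict ones at once.

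**3. Whether exclusion counts work for criteria unrelated to the route.** Suppose a criterion excludes 10% of enquirers (assumed). The exact binomial probability of seeing at least 5 exclusions is 0.88 with 75 enquirers, 0.98 with 100 and 0.999 with 150. A restrictive rule on cognition, stable medication, concurrent therapy or prior mindfulness training would normally show.

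**4. Whether they work for home access.** Let q be the share of people with PD who lack a home computer or internet, and r their chance of being reached by the adverts or email relative to everyone else. The share of enquirers failing the criterion is q·r/(q·r + 1 − q). Neither q nor r is in the documents, so ranges are shown. Expected exclusions per 100 enquirers:

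| q | r = 0 | r = 0.02 | r = 0.05 | r = 0.10 | r = 1 (reached equally) |
|---|---|---|---|---|---|
| 10% | 0 | 0.2 | 0.6 | 1.1 | 10 |
| 20% | 0 | 0.5 | 1.2 | 2.4 | 20 |
| 30% | 0 | 0.8 | 2.1 | 4.1 | 30 |
| 40% | 0 | 1.3 | 3.2 | 6.3 | 40 |

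Worked cell: q = 0.20, r = 0.05 gives 0.01/(0.01 + 0.80) = 0.0123, or 1.2 per 100. With q = 0.20 and r = 0.02, the probability that 100 enquirers include no access exclusion at all is (1 − 0.0050)^100 = 0.61. The logged count depends heavily on r, which the pilot does not observe, so it cannot be turned back into q.

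**The case against.** The strongest reply is that the plan does not rest on the target alone. The same sentence adds exclusions by criterion, and step 2 shows that these separate the very scenarios the target confuses. This stands. A reader might infer that the planned assessment cannot detect restrictive criteria at all; the second half of the sentence and step 3 contradict that. A clear recruitment shortfall would also be a signal, though not a specific one.

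A reader might also fault the use of adherence and retention, since these are seen only in people who were admitted. The article uses them for a different question, whether the people recruited are receptive to and suited for the course, and enrolled participants can answer that. Nor would looking at attendance by cognitive score among those enrolled settle the cognitive cut-off, because nobody below the cut-off would be in the data.

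Third, the access criterion follows from a course delivered over Skype, the advisory groups were on balance in favour of Skype, and nowhere does the article say it will declare this criterion unrestrictive. That is fair and limits the consequence. It does not make a low exclusion count informative.

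Fourth, a recruitment route confined to people already online is partly inference. The second foundation's medium is not given, and someone may hear by word of mouth, or be online by phone or shared access without a home computer. So near-zero counts are likely, not certain. The r = 0.10 column allows for some of this, and the counts remain far below those under equal reach.

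**Conclusion.** The point holds in a limited form and is minor. Recruitment against target measures recruitment feasibility and cannot separate strict criteria from advert reach or consent. Exclusions by criterion can reveal restrictiveness among enquirers for most criteria, but not for home computer/internet access under the recruitment route described.

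For that criterion, about 0 to 3 exclusions per 100 enquirers would be expected if people without access are reached at most 5% as readily as others, and up to about 6 at 10%, against 10 to 40 under equal reach. These figures rest on assumed values of q (10% to 40%) and r. The direction does not depend on the exact values, only on people without access being much harder to reach by web advert and email. The text supports that assumption without proving it.

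**What to change.** In Feasibility outcomes:

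1. Treat recruitment against target as a measure of recruitment feasibility only.
2. Base the conclusion on restrictiveness on the number excluded on each criterion, divided by all people screened.
3. State that the home computer/internet criterion cannot be evaluated under this recruitment route, so few or no exclusions on it are not evidence that it is unrestrictive.
4. Limit the feasibility and accessibility conclusions to people with PD who are already largely online, and add this to the limitations in the Discussion.

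The cost is a few sentences and one table from the screening records, with no new data collection. The downside is a narrower stated conclusion on accessibility.
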